#### Economic evaluation

The following health economic analyses will be conducted:

Cost-consequences analysis with costs encompassing health care, social care and education, presented in a disaggregated manner.Cost-effectiveness expressed as incremental cost per additional case of child protection or out-of-home care avoided.

the economic evaluation of FGCs will be conducted from a public sector perspective. Primary micro-costing will be undertaken in WP2 via the practitioner questionnaire to estimate the cost of delivering FGCs across service model delivery types and geographical settings, including the costs of the identification and referral processes, training of accredited providers, delivery of sessions in alternative formats, participant monitoring activities and any follow-up/management. Where applicable the unit costs of resource inputs will be estimated in accordance with the principles of opportunity costs.

Broader health care, social care and education resource use over the follow-up period will be extracted from HES and NPD records and costed using national reference cost schedules. Resource use will be measured by the number and where possible, the duration of admissions, appointments and attendances during the 2-year follow-up period. Mean differences in children’s health and social care use and special educational needs provision and their associated costs (between the intervention and control arms) will be estimated using t-tests and bootstrap 95% confidence intervals that will be computed based on 1,000 (or more) replications.

The primary objective of the health economic evaluation is to estimate the incremental cost per additional case of child protection or out-of-home care avoided. Bivariate regression of costs and consequences, with multiple imputation of missing data (e.g., as a result of loss to follow-up), will be conducted to generate within-study estimates of incremental cost-effectiveness associated with FGCs.

A cost-consequences analysis will additionally be conducted, and we will present disaggregated costs and disaggregated consequences (outcomes 1 to 3 above), together with the estimates of the mean costs of the comparator interventions with appropriate measures of dispersion. Cost-consequences analyses are recommended for complex interventions that may have multiple implications [46], and for public health interventions which may have an array of benefits that are difficult to synthesise in a common unit [47].

Our analytical strategy will be informed by recent guidance on accounting for selection biases within economic evaluations using individual patient level observational data [48]. A key methodological challenge will involve generating expressions of cost-effectiveness amenable to broader cost-effectiveness comparisons by decision makers. A range of economic values for avoiding adverse child welfare outcomes will be informed by a review of the revealed and stated preference literature related to children’s social care, as well as by WP1. A series of sensitivity analyses will be undertaken to explore the implications of uncertainty on the incremental cost-effectiveness ratios.

Fig 1 illustrates the relationship between the three work packages. They connect insofar as WP2 and WP3 each assess different elements of the programme theory developed in WP1. Family-reported mechanisms, context and outcomes will be assessed in WP2. Outcomes related to service use (e.g., reduced state intervention to prevent child maltreatment) and some aspects of context (e.g., local authority) will be assessed in WP3.

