### Work Package 3: Comparison of service use and associated costs in FGC participants and a comparison group after two years using a quasi-experiment (RQ4)

Public-facing title: Service use study (Family VOICE project)

WP3 is a quasi-experiment to assess service use outcomes of FGCs and the economic dimension of these. The experimental dimension is comparison of families who have had FGCs with similar families in local authorities with no FGC provision. This work package will assess some longer-term outcomes from the programme theory developed in WP1 for which administrative data are more suitable than self-report, because of the need for complete coverage of the relevant population without social desirability bias.

Outcomes to be measured include:

1. Primary outcome

The primary outcome is whether category (of seriousness) of children’s social care intervention at two years after FGC (or equivalent date for comparison group) is the same level, lower or higher than at the time of FGC. A ladder of escalation will be used, with state intervention categories ordered from most to least serious, including the child having been:

categorised as in need (and reason for this);subject to a child protection investigation;on a child protection plan;looked after by the local authority (and, if so, on what legal basis; type of care–foster, kinship, residential, placed with parents).

The primary outcome variable will be binary, describing whether the category of statutory intervention at 2 years after FGC (or equivalent date for the non-FGC group) is the same or lower than at the time of FGC (or equivalent date) or whether it is higher.

2. Secondary outcomes

Highest category of children’s social care intervention since the FGC (or equivalent date for comparison group) at any time during the two-year follow-up.

A summary measure of duration and seriousness of all children’s social care intervention during follow-up.

Health care use for health conditions and events which might potentially be affected by FGC attendance–e.g., child and parent mental health, serious injury to a child, assault resulting from domestic abuse:

hospital admissions;outpatient appointments;‘Improving Access to Psychological Therapies’ [39] services;community mental health services;accident and emergency attendances.

Absence from school and special educational needs provision.

Incremental cost per adverse social-care-outcome-adjusted year avoided.

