#### Sampling, settings and research participants

Families who have attended FGCs will be identified by local authorities–we will work with several large authorities in England, and access anonymised data from the Department for Education, NHS Digital and the Office for National Statistics (ONS). This part of the study is not linked in any way to the WP2 families. In these participating local authorities, we will also access routine data on families who have been referred to children’s services but have not had an FGC, in order to delineate the circumstances in which families do and do not take part in FGCs in these particular authorities.

A comparison group of local authorities which do not offer FGCs will be identified in the WP1 survey. Families from these authorities will be identified from the Children in Need Census. This part of the study uses data from only one UK country–England–because the datasets are different for each nation and given the complexity of data linkage it would not be feasible to attempt this study in more than one nation. We have chosen England as having the largest population.

Eligible families will be those with at least one child under 18 years of age referred to departments of Children’s Social Care Services from 1.1.17 to 31.12.19 at participating local authority sites in England (there is no intention to connect these local authorities to those taking part in earlier work packages). No additional exclusion criteria will be applied. At this stage we are not imposing a lower age limit. However, although we are confident that linkage to health records for school-age children is viable, there is some uncertainty about this linkage for pre-school children. We will therefore have to test the feasibility of extending the age profile to include all children from birth, in the early stages of WP3.

To make the two groups of families from different local authorities comparable for analysis, we will use statistical techniques to improve balance across the two groups for several known confounders. We will use propensity score weighting [40, 41] to estimate the average ‘causal’ effect of having an FGC on the outcomes.

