#### Data analysis

We will use Stata or R software to estimate a family’s propensity for having an FGC with a logistic regression on variables including stage of the child welfare process (referral, child in need, child protection assessment, child protection plan), reason for referral and family demographics. The analysis model for the primary outcome variable (whether the level of social care intervention at two years after the FGC–or equivalent baseline date for the control group–has increased or not) will be two-level logistic regression, with random effects for local authorities and weighting of families according to their propensity for having an FGC. Fixed effects will include intervention (whether a family has had an FGC or not) as well as other factors–to be determined in WP1 –to account for the different ways FGCs are set up in different local authorities. Effect estimates will be presented with two-sided 95% confidence intervals and p-values. Secondary outcomes will be analysed using the same propensity score weighting approach and appropriate two-level regression models depending on the type of outcome variable (e.g., logistic for binary outcomes, linear for continuous outcomes).

We will undertake multiple imputation to explore the impact of potential missing data. We will also consider alternative covariate balancing or matching methods, such as entropy balancing [43], Mahalanobis distance matching [44] and coarsened exact matching [45] if propensity score weighting does not achieve good enough covariate balance and/or as sensitivity analyses. Detailed statistical analysis plans for WP2 and WP3 will be finalised prior to any analysis being performed, and these will be published on the study website.

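### The t-tests and bootstrap intervals set for WP3 service-use and cost differences conflict with the propensity-weighted two-level analysis promised for WP3 outcomes

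*Protocol article*

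**What the plan says.** All references are to WP3 in the protocol article.

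- **Design.** The experimental element is a "comparison of families who have had FGCs with similar families in local authorities with no FGC provision". Allocation is not random, and the comparison families sit in different authorities from the FGC families.
- **Adjustment (Sampling, settings and research participants).** To make the groups comparable, "we will use statistical techniques to improve balance across the two groups for several known confounders". The section continues: "We will use propensity score weighting [40, 41] to estimate the average ‘causal’ effect of having an FGC on the outcomes".
- **Primary outcome (Data analysis).** The model is "two-level logistic regression, with random effects for local authorities and weighting of families according to their propensity for having an FGC".
- **Secondary outcomes (Data analysis).** "Secondary outcomes will be analysed using the same propensity score weighting approach and appropriate two-level regression models depending on the type of outcome variable". The outcome list at the start of WP3 puts health care use, special educational needs provision, a summary of social care intervention and an incremental cost measure under this heading.
- **Use and cost differences (Economic evaluation).** The sentence opens "Mean differences in children’s health and social care use and special educational needs provision and their associated costs (between the intervention and control arms" and says that these "will be estimated using t-tests and bootstrap 95% confidence intervals that will be computed based on 1,000 (or more) replications". It names no weights, covariates or local-authority level.
- **Cost-effectiveness (Economic evaluation).** The incremental cost per case avoided comes from a bivariate regression of costs and consequences with multiple imputation. Its weights and clustering are not stated.
- **Selection bias (end of Economic evaluation).** "Our analytical strategy will be informed by recent guidance on accounting for selection biases within economic evaluations". No method is named.

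**The concern.** A two-sample t-test compares raw group means and assumes independent observations. That suits a trial that randomises individual families. Here the comparison families may be any family referred in 2017 to 2019, with no further exclusions, in authorities that do not offer FGCs. The protocol puts stage of the child welfare process first among its propensity variables, and stage plausibly drives social care use and cost directly. An unadjusted difference mixes any FGC effect with differences in stage, reason for referral and family demographics. The direction of that bias cannot be told from the document.

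Exposure also differs between authorities, so variation between authorities feeds straight into the group difference. The Data analysis section allows for this with random effects. The economic section is silent on it.

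Research question 4 asks how service use compares with similar families and what the economic consequences are. The mean cost and use differences are natural material for the cost-consequences analysis. Someone writing the detailed plan cannot follow both sections for health care use and special educational needs provision. For mean costs, the t-test and bootstrap sentence is the only method stated specifically for the group difference.

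**Working it through.** **1. The plan's own figure.** The only numerical WP3 design figure is a detectable difference of 10.5 percentage points for a binary outcome, with 300 and 1000 families, proportions near 0.5, 90% power and two-sided 5%.

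(1.960 + 1.282) × √[0.25 × (1/300 + 1/1000)] = 3.242 × 0.0329 = 0.107.

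Solving the power formula exactly gives 10.6 points, and power at 0.50 against 0.605 is 89.7%. The figure reproduces to rounding and is not disputed. It treats families as independent. No intracluster correlation (ICC), number of authorities or precision target for costs is given.

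**2. The stated analyses side by side.**

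| Quantity | WP3 outcome list and Data analysis | Economic evaluation |
|---|---|---|
| Health care use | Secondary outcome: weighted, two-level | t-test, bootstrap interval |
| Special educational needs provision | Secondary outcome: weighted, two-level | t-test, bootstrap interval |
| Social care use | Summary of duration and seriousness is a secondary outcome: weighted, two-level | t-test, bootstrap interval |
| Mean costs | Not listed separately | t-test, bootstrap interval |
| Incremental cost per case avoided | A related incremental cost measure is a secondary outcome | Bivariate regression, weights and clustering unstated |

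The first two rows conflict outright and the third very nearly does. In the fourth, the specific sentence departs from the general commitment to weighting. The fifth is silence, not conflict.

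**3. Size of the clustering effect if families are treated as independent.** Inputs: 300 and 1000 families (protocol). Assumed: 6 FGC and 20 comparison authorities, which is 300/6 = 1000/20 = 50 families each, of equal size. Variance inflation is 1 + (50 − 1) × ICC. It is the same in both groups, so the standard error ratio is its square root. Coverage of a nominal 95% interval is 2Φ(1.96/ratio) − 1.

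| Assumed ICC | Inflation | Standard error ratio | Coverage |
|---|---|---|---|
| 0.01 | 1.49 | 1.22 | 89% |
| 0.02 | 1.98 | 1.41 | 84% |
| 0.05 | 3.45 | 1.86 | 71% |

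Over a wider range (10 comparison authorities, 3 to 10 FGC authorities, ICC 0.005 to 0.05), the ratio runs from 1.11 to 2.44 and coverage from 92% to 58%. These figures ignore any further loss of precision from weighting.

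**4. Size of the confounding effect if no adjustment is made.** The protocol gives no imbalance, so this is illustration only. Bias in standard deviations (SD) of cost = standardised imbalance in baseline seriousness × its correlation with cost. The independent-families standard error is √(1/300 + 1/1000) = 0.0658 SD. With an assumed correlation of 0.3:

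- imbalance 0.1: bias 0.03 SD, 0.46 standard errors, coverage about 93%
- imbalance 0.2: bias 0.06 SD, 0.91 standard errors, coverage about 85%
- imbalance 0.5: bias 0.15 SD, 2.28 standard errors, coverage about 38%

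**The case against.** Much of the right analysis is already promised. The sampling section commits WP3 to propensity weighting, and the Data analysis section extends weighted two-level models to the secondary outcomes, which cover most of the use quantities in the t-test sentence. The economic section itself says it will be guided by work on selection bias. Detailed plans for WP2 and WP3 are to be finalised before any analysis and published, and an article may leave detail to them. A bootstrap can carry weights and can resample authorities; the text does not say it will do otherwise.

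This narrows the point but does not remove it. The existing commitments are what make the t-test sentence a contradiction. It names a method; it does not leave one open. The selection-bias remark names no method, does not withdraw the t-tests and does not deal with clustering.

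Three stronger readings are tempting, and the document does not support them:

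- *All the economic results are confounded.* The t-test sentence covers only mean differences in use and cost. The main economic objective uses bivariate regression, whose weights and clustering are unstated, not excluded.
- *The cost and effect parts of the cost-effectiveness ratio would come from differently adjusted populations.* They are estimated together in one regression, and nothing says the t-test differences feed into it.
- *The bootstrap is unweighted and resamples single families.* Neither the weighting nor the resampling unit is given. The clustering figures therefore depend on families being treated as independent.

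**Conclusion.** The point holds as an internal conflict over a stated method. The economic section's t-tests and bootstrap intervals do not match the weighted two-level analysis that the sampling and Data analysis sections set for WP3 outcomes, including two quantities named in both places. If the t-test sentence is followed, the use and cost differences are unadjusted for confounders that the study will have measured. If families are also taken as independent, standard errors are understated by about 1.2 to 1.9 times at an ICC of 0.01 to 0.05 with 50 families per authority. The ICC, the number of authorities and any baseline imbalance are assumptions, so the sizes are indicative. The conflict itself rests on the text alone. It should be settled before the WP3 analysis plan is finalised.

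**What to change.** In the Economic evaluation section and the WP3 analysis plan:

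1. Replace the t-tests with the propensity-weighted comparison from the Data analysis section: a weighted regression of cost or use on FGC.
2. Allow for clustering with local-authority effects, or with a bootstrap that resamples authorities within each group and re-estimates the propensity weights in every replicate. If only a few authorities take part, a bootstrap over authorities will itself be rough, and the plan should say so.
3. State that the bivariate cost-consequence regression uses the same weights and clustering.
4. Keep unadjusted means and differences as description only.

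The cost is wording, some extra computing and probably wider intervals. No new data are needed, because the weights and the authority identifiers are already required for the primary outcome.

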**Fig 1 pone.0300834.g001:**
[figure not shown]
Flow chart of study work packages.

### Ethics and governance

All elements of WP1 have ethical approval from the UK Health Research Authority’s Social Care Ethics Committee (REC reference 22/IEC08/0003). WP2 has ethical approval from the UK Health Research Authority’s Social Care Ethics Committee (REC reference 3/IEC08/0029). WP3 has been approved by the South West–Cornwall and Plymouth Research Ethics Committee (REC reference 22/SW/0144). Approval has been given for the whole study by the Association of Directors of Children’s Services Research Group for England and initial support from the Northern Ireland Health and Social Care Board. No such national approval exists in Wales or Scotland.

Local authority records will be accessed without consent under General Data Protection Regulation (GDPR) Article 6(1). We consider this research to be of public interest. The proposed WP3 data flow from LAs to DfE is already covered by existing legal remits (under section 83 of the Children Act 1989. All individual-level linked project data will be pseudonymised and stored at the ONS-SRS.

A Project Steering Committee has been established to bring independent academic and sectoral expertise. The Chair is an experienced social work academic, and the committee includes methodologists, a statistician, a representative from the Family Rights Group who quality assure FGCs, and a civil servant working in national child and family policy. It will meet once a year throughout the project. As mentioned earlier, a Families’ Research Advisory Group will also run throughout the project, in parallel to the Project Steering Committee.

## Discussion

The study is an example of a pragmatic evaluation of an existing intervention, to identify what mechanisms and contexts influence effective process and longer-term outcomes [49]. Its strengths are the inclusion of an element of co-design with both family members and practitioners, and comparisons, both internally, within a pool of FGCs from different contexts, and externally, with families who did not have FGCs because they were not offered in their areas. Limitations include consulting with families in only two UK sites in WP1, the lack of a comparison group in WP2, and the potential for baseline differences in unknown or unmeasured confounders between the two groups being compared in WP3.

The study’s original contribution will be helping to explain variation in family-reported outcomes in terms of their relationship with mechanisms and context (WP2); and one of the longest follow-up periods of any FGC study (WP3), using administrative data with good quality coverage and fewer selection issues than in questionnaire studies. Findings from these work packages should be of use for policy and practice, as well as the programme theory developed in WP1, the mapping of UK services, and the WP2 questionnaires that will be available for future use in routine practice.

It is worth noting some unexpected practical barriers encountered, for other researchers undertaking UK-wide studies in this field. Firstly, it is important for social care researchers to note that the Northern Irish social care system is joint with the health service. This means that in applying for ethical approval, it is in fact incorrect to describe a UK-wide social care research project as not taking place in the NHS, even though it is not assessing a health care intervention, and even where no NHS data are involved (as for our WP1). In the case of Northern Ireland, the setting is classed as both social care and NHS because of the structure of services. There are additional processes and permissions associated with research in the NHS that some social care researchers may not be familiar with.

To approach individual social services departments in Wales and Scotland, there is no national prior approval needed. In England and Northern Ireland there are additional national processes, but these have different outputs. In England, approval from the Association of Directors of Children’s Services gives researchers permission to contact individual local authorities, although there is a cost attached–a sliding scale depending on the size of the research grant. In Northern Ireland, initial approval is needed from the Northern Irish Health and Social Care Board, but this does not in fact constitute approval to approach each local trust. Each one must agree this separately and the process is similar to the NHS research governance process in the rest of the UK.

Another barrier that is useful for other research teams to know about is that the UK National Social Care Research Ethics committee took the view that parents involved in care proceedings should either be excluded from WP1 workshops, or it should be explained to them that anything they said could be used in court. Considering this stance, we decided to exclude this group of parents, on the basis that the context of family court proceedings might make discussion about their circumstances emotionally difficult. However, the idea that any involvement of such parents in research would mean their words could be used in court has wider implications that need discussion with the committee and within the community of social care researchers.

It should be acknowledged that recruitment to the ‘Family views and context study’ (WP2) will be challenging, as it relies on multiple co-ordinators in several different FGC services recruiting multiple family members. As noted earlier, a recruitment and retention protocol, informed by evidence on successful strategies, will be used to support the process, including the use of financial incentives. It is nonetheless possible that in some services insufficient numbers of families will be recruited and small sample sizes will preclude site-specific feedback.

Any essential amendments to the protocol will be agreed by the Project Steering Group and research funders and then published on the funder’s study website.
